***Screening Interview***							
Orientation, Memory and Concentration Test (OMC)	I	X					
Diagnostic Interview for Anxiety, Mood, and OCD and Related Neuropsychiatric Disorders (DIAMOND)	I	X					
Columbia Suicide Severity Rating Scale (C-SSRS)	I	X					
Structured Clinical Interview for Sleep Disorders—Revised (SCISD-R)	I	X					
***Primary Outcome Measures***							
Montgomery-Asberg Depression Rating Scale (MADRS)	I		X	X	X		X
Young Mania Rating Scale (YMRS)	I		X	X	X		X
Brief Quality of Life in Bipolar Disorder (QoL.BD)	SR		X	X	X	X	X
***Secondary Outcome Measures***							
Longitudinal Interval Follow-up Evaluation (LIFE)	I			X	X		X
Patient Mania Questionnaire (PMQ-9)	SR		X	X	X	X	X
Patient Health Questionnaire (PHQ-9)	SR		X	X	X	X	X
Patient Global Impression (PGI)	SR			X	X	X	X
Clinician Global Impression (CGI)	I			X	X		X
*Optional:* EMA of Emotion States: Mood Zoom (MZ)	App		7 days		7 days		
WHO Disability Assessment Schedule 2.0-Brief	SR		X		X		
General Anxiety Disorder-7 (GAD-7)	SR		X		X		
Rapid Measurement Toolkit-20 (RMT20) panic, social anxiety and PTSD subscales	SR		X		X		
Godin Shephard Leisure-Time Physical Activity Index	SR		X		X		
***Intervention Acceptability Probes***							
Ratings of the acceptability of the Intervention	SR				X		
***Adherence***							
Food Logging	SR		Daily	Daily			10 days- first & last intake
Sleep Household Environment and In-Bed Behaviors	SR		X		X		
***Potential Mechanisms of Change***							
Continuous glucose monitoring	HC		2 weeks	2 weeks starting week 7			
Actigraphy/Distal Temperature	HC		2 weeks	3 weeks starting week 7			
Metabolic Panel	QD		X	X			
Glucose Tolerance Test	QD		X	X			
DLMO	HC		X	X			
Clock Genes	HC		X	X			
Inflammation	HC		X	X			
Core Consensus Sleep Diary (CORE CSD)	SR		10 days	10 days			
PROMIS: Sleep Disturbance and Sleep-Related Impairment Scales	SR		X	X	X		X
***Potential Moderators***							
Positive Urgency Scale	SR		X		X		
Household Food Security Survey (HFSSM)	SR		X				
Menopause QoL items on sleep disruption (for women ages 45–65 (MENQoL)	SR		X				
Food Frequency Questionnaire (FFQ)	SR		3 days	3 days			
Somatotherapy	SR	X	X	X	X	X	X
Demographics	SR		X				
Credibility and Expectancy Questionnaire – Credibility Set	SR		X				

*App* Application, *I* Interview, *SR* Self-report, *HC* Home collection, *QD* Quest Diagnostics

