##### Secondary hypotheses

H4. TRE adherence will predict improvements in self-rated symptoms of mania and depression at 10 weeks and 6 months post-baseline compared to baseline symptom severity scores.H5. The degree of change in sleep and the amplitude of diurnal activity/distal temperature rhythms at week 8 will explain improvement in symptoms (week 10), controlling for baseline symptoms and sleep/diurnal rhythm amplitude.H6. The degree of change in metabolic health (CMP) at week 8 will explain improvement in symptoms (week 10), controlling for baseline symptoms and metabolic health.

To provide a more refined index of changes in emotion, we will assess the effects of TRE on daily emotional lability (as assessed using EMA, baseline and post-intervention).

We will conduct exploratory analyses to examine secondary outcomes (e.g., EMA) and potential moderators.

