### Trial design

The trial is a non-randomized, single arm (TRE) study. The primary endpoint is immediately after the 8-week-long TRE period (end of week 10). The follow-up assessments will be conducted at 6 months after the baseline, supplemented with post-baseline self-reported assessment at week 16. Hypothesized mechanisms of change will be tested at baseline and at 8 weeks post-baseline. The study setting is remote (online food plan materials, questionnaires, and interviews), supplemented with at-home collection of biological data (DLMO, clock genes, actigraphy, CGM) and assays completed by Quest Diagnostics (CMP, glucose tolerance test).

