#### Primary outcomes

Our primary outcome measures will be: interview-based assessments of mood symptoms, and a brief self-report measure of Quality of Life, which were chosen based on strong psychometric characteristics, including high interrater reliability for the interview-based measures. Where possible, the symptom severity interviews will be conducted by raters who are unaware of the participant’s intervention status (which is feasible as our team is conducting a parallel study involving the Mediterranean diet). Where a rater becomes inadvertently aware of the intervention status, we will attempt to replace the interviewer for that participant.

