#### Potential moderators

We will gather several variables to assess their role in moderating outcomes. These include data on the types of psychotropic and sleep medicines, doses, and adherence levels at each self-report assessment to calculate summary scores for each major receptor type. At baseline, we will gather data on the Positive Urgency Scale [128], food insecurity (HFSSM; [94, 129]), and Menopause QoL sleep items [96, 97], as potential predictors of intervention outcome. At baseline and at 6 weeks, we will gather a Food Frequency Questionnaire to assess inadvertent changes in dietary intake (e.g., less dessert consumption after participants stop midnight snacks).

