### Statistical analysis plan

Before conducting analyses of hypotheses, we will examine whether values appear to be missing at random. If this missing value imputation assumption is supported, we will impute data using 20 resamples, using demographic (sex/gender, age), baseline symptom severity, and symptom history variables (number of episodes) to predict missing scores. For comparison, we will perform analyses without imputed values. Data cleaning will be completed as described above in data quality. Statistical analyses will be conducted in accordance with the International Conference on Harmonization E9 statistical principles.

Before conducting analyses of hypotheses, we will carefully examine potential confounds. We will avoid adding any covariates that were entangled with our core mechanisms (e.g., sleep and circadian processes). With this in mind, we will only consider covariates for inclusion in models if they could be confounding our main effects– that is, those that are significantly correlated with both our IV (treatment adherence) and DVs (symptoms and QoL). Power analyses were based on inclusion of two covariates, and we would hope not to exceed this number of covariates. If more than two potential covariates are identified that appear significantly and uniquely correlated with both the IV and DVs, we would redo our power analyses, but at this point, we would be able to consider the covariance matrices, allowing for more careful estimation of true statistical power. We would consider these issues without generating the models of how our treatment variables actually influence symptoms and QoL, so as to avoid p-hacking or “fishing”. Only if those power analyses suggested that we could include more than 2 variables as confounds would we proceed to add more covariates; otherwise, we would plan to choose the two covariates that appear to hold the highest unique correlations with IV and DVs.

Analyses will be conducted using two-tailed tests with alpha set to .05.

Our core hypotheses will be tested using two parallel structural equation models (SEM) to consider mania and depression separately. In each, we will examine paths from TRE adherence levels to a latent variable for clock gene amplitude (based on 3 genes) to symptoms to QoL, controlling expected covariates and evaluating the potential confound of glucose tolerance mediation.

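### Baseline treatment credibility should be a fixed covariate in the adherence-to-symptom and adherence-to-QoL equations, because the planned significance screen may leave it out

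*Protocol article*

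**What the plan says.** All references are to the protocol article.

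- **Design.** "The trial is a non-randomized, single arm (TRE) study" (Trial design).
- **Exposure.** Adherence is the share of adequately logged days on which the eating-window goal was met (TRE adherence). It comes from participants' own food logs, to which missed entries can be added later (Food logs).
- **Outcomes.** The primary outcomes are the interviewer-rated MADRS and YMRS, with raters masked to the intervention where possible, and "a brief self-report measure of Quality of Life" (Primary outcomes). H3 is an indirect effect of adherence on QoL through symptoms (Hypotheses). H4 states that "TRE adherence will predict improvements in self-rated symptoms of mania and depression at 10 weeks and 6 months post-baseline" (Secondary hypotheses).
- **Belief in the treatment.** Table 1 lists "Credibility and Expectancy Questionnaire – Credibility Set", at baseline only, in the potential moderators block. No expectancy set is listed. The text section on moderators opens "We will gather several variables to assess their role in moderating outcomes" and does not name credibility.
- **Covariates.** The statistical analysis plan section considers as covariates only "those that are significantly correlated with both our IV (treatment adherence) and DVs (symptoms and QoL"). It also says: "We will avoid adding any covariates that were entangled with our core mechanisms", giving sleep and circadian processes as examples. On number: "Power analyses were based on inclusion of two covariates". If more than two candidates appear and a new power analysis does not allow more, the two with the highest unique correlations are kept.

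**The concern.** Nobody is randomized to a level of adherence, so whatever makes people adhere is carried into every adherence path. Participants who believe TRE will help may follow it more closely, log it more carefully and report more improvement. That is confounding by a variable measured before TRE begins. Testing credibility as an interaction with adherence asks whether the slope differs by belief; it does not remove the bias from the slope.

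The covariate rule offers a second way in, but entry depends on significance tests in about 125 people. A confounder can bias the adherence estimate while failing one of those tests. Credibility must also compete for one of about two places. At stake is how far an adherence association in H4, or in the adherence-to-symptom part of H3, can be read as an effect of eating timing and not of belief.

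**Working it through.** **Inputs from the protocol article.** 150 recruited − 25 lost = 125 analysed; two-sided alpha .05. The article gives no figure for expectation, credibility or their correlations, so there is no stated figure to reproduce on this point. The stated power of .81 concerns the path from amplitude through symptoms to QoL and is not used here.

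**Assumptions.** Expectancy E correlates r with adherence A and r with self-rated improvement Y. Credibility C correlates ρ with E. There is no true effect of A on Y.

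**Formulas.**
- Unadjusted: corr(A, Y) = r².
- Adjusted for C: partial correlation = (r² − r²ρ²) / (1 − r²ρ²).
- Rejection rate: 1 − Φ(1.96 − δ) + Φ(−1.96 − δ), where δ = √(n − 3) × atanh(correlation), with n − 4 when adjusting for C.
- Screen: corr(A, C) = corr(Y, C) = rρ. The chance that C passes is the rejection rate at rρ, squared. This treats the two tests as independent and uses a single outcome.

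**At r = .3.**
- Unadjusted: correlation .09; δ = √122 × .0902 = 1.00; rejection 17%.
- Adjusted, ρ = .5: (.09 − .0225) / (1 − .0225) = .069; δ = 11 × .069 = .76; rejection 12%.
- Adjusted, ρ = .7: (.09 − .0441) / (1 − .0441) = .048; δ = .53; rejection 8%.
- Screen, ρ = .5: rρ = .15; δ = 1.67; each test passes with probability .386; .386² = 15%.
- Screen, ρ = .7: rρ = .21; δ = 2.35; each test passes with probability .653; .653² = 43%.

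**Range.**

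| r | Falsely significant, unadjusted | Adjusted for C (ρ = .5 / .7 / .9) | C passes screen (ρ = .5 / .7 / .9) |
|---|---|---|---|
| .2 | 7% | 6% / 6% / 5% | 4% / 12% / 27% |
| .3 | 17% | 12% / 8% / 5.5% | 15% / 43% / 75% |
| .4 | 43% | 28% / 16% / 7% | 37% / 79% / 97% |
| .5 | 81% | 61% / 36% / 10% | 65% / 96% / >99% |

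A separate simulation (3,000 trials of 125, ρ = .5 and .7) agrees. At r = .3 it gives 16% unadjusted, 8% to 11% adjusted and 16% to 45% passing the screen. At r = .4 it gives 43% unadjusted and 16% to 27% adjusted. At r = .2 it gives 8% unadjusted and 7% adjusted.

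**Serial path.** In the core model adherence acts through clock-gene amplitude. Expectation then distorts the amplitude-to-symptom link only by (adherence-amplitude correlation) × r². Assuming .3 to .4 for that correlation and r = .3, this is .3 × .09 = .027 to .4 × .09 = .036. Then δ = .30 to .40, and rejection is about 6% to 7%.

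**The case against.** The strongest reply is that the plan already has a confounder rule. Baseline credibility is eligible under it, because it is not a sleep or circadian variable. The moderator heading does not fix its analytic role either: demographics sit in the same block, and sex/gender and age are also used for imputation. This stands. A reader might infer from Table 1 that credibility can be used only as a moderator and that the bias cannot be removed. The documents do not support that, and the adjusted figures above show partial removal.

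A second reply is that the calculation describes a direct adherence-to-outcome test, while H3 is indirect and the core model runs through a laboratory measure. The primary symptom scales are also rated by interviewers masked where possible. This stands too. The 16% to 17% fits H4 and any direct adherence-to-outcome equation, not the serial path. Masked raters do not help the self-rated scales, and interview ratings still depend on what unmasked participants report.

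A third is that the size rests on assumed correlations. At r = .2 the inflation is small. At r = .4 or more with ρ of at least .7, the screen usually admits credibility. The gap therefore matters mainly in between, or when credibility is a weaker proxy for expectancy.

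Finally, covariate choice could be left to a statistical analysis plan that is not shown. But the article does state a rule, and that rule is what makes adjustment uncertain.

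**Conclusion.** The point holds in limited form. Belief in TRE is a plausible confounder of the adherence-to-symptom and adherence-to-QoL associations. A baseline measure of it is collected, and the stated rule does not ensure that it is used. At r = .3 and ρ of .5 to .7, the screen would omit it in roughly 55% to 85% of trials. A direct test on a self-rated outcome would have a false-positive rate of about 16% to 17% unadjusted against 8% to 12% adjusted. These rates are for analyses that never or always adjust; the rate for the two-step procedure was not computed. All the correlations are assumptions.

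Two stronger readings should be resisted. One is that the trial's main mechanistic test is undermined: the path through clock-gene amplitude is only slightly exposed (about 6% to 7%), and H1 has a laboratory outcome. The other is that collecting expectancy would restore the 5% rate. That result needs expectancy measured without error. A real subscale is also an imperfect proxy, and the trial has no control arm.

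**What to change.** 1. Pre-specify baseline credibility as a fixed covariate, outside the significance screen, in the adherence-to-symptom and adherence-to-QoL equations (H4 and the adherence-to-symptom part of H3). A moderator analysis can be kept alongside.
2. Describe these paths as associations.
3. Optionally, add the expectancy items of the same questionnaire to the baseline survey for those still to be enrolled, and adjust for them in a sensitivity analysis. Those already enrolled would have credibility alone. This reduces the bias but does not remove it.

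The first two changes cost a few sentences, because the score is already collected. The real price is in the covariate allowance: credibility takes one of the two places on which power was based, leaving one for the screen. Expectancy, if added to the same model, would take the other, which is a reason to keep it to a sensitivity analysis. The third change also adds a few self-report items.

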#### Screening questionnaires

All screening questionnaires are well-validated, commonly used indices.

##### DIAMOND Self Report Screener psychosis subscale [103]

We will administer the DIAMOND Self Report Screener psychosis subscale to assess psychotic symptoms. For individuals who endorse at least one symptom, we will administer the DIAMOND psychosis module to further evaluate participant eligibility.

##### Alcohol Use Disorder Identification Test (AUDIT; [104–106])

We will administer the AUDIT to screen for alcohol use symptoms. For individuals who score above the threshold on the AUDIT (≥ 8), we will administer the DIAMOND alcohol use disorder module to further evaluate participant eligibility.

##### Drug Use Disorder Identification Test (DUDIT; [107, 108])

We will administer the DUDIT to screen for drug use symptoms. For individuals who score above the threshold on the DUDIT (≥ 6 for men; ≥ 2 for women and nonbinary individuals), we will administer the DIAMOND substance use disorder module to further evaluate participant eligibility.

##### Insomnia Severity Index (ISI; [78, 80])

The ISI is a 7-item index of insomnia symptoms, including sleep disturbance and daytime consequences of poor sleep.

##### Short Eating Disorder Examination Questionnaire (EDE-QS; [83])

The EDE-Q short form is a 12-item self-report measure designed to assess a range of eating-related symptoms, including restraint, eating concern, shape concern and weight concern [109]. The EDE-QS has shown strong internal consistency (Cronbach’s α = .913, high temporal stability (ICC = .93), and high correlations with eating disorder diagnoses and original EDE-Q scores (r’s > 0.81).

##### Munich Chronotype Questionnaire (MCTQ; [110])

The MCTQ is designed to assess chronotype, with a focus on sleep timing during free days.

##### Brief Social Rhythms Scale (BSRS; [111])

The BSRS assesses the irregularity of engagement in daily activities such as mealtimes and social interaction on workdays and free days, and has been validated in BD.

#### Screening interviews

Our chosen Interviews have all been shown to have strong inter-rater reliability and validity.

##### Orientation Memory Concentration test (OMC; [112])

The OMC is a brief test of mental status.

##### Diagnostic Interview for Anxiety, Mood, and OCD and Related Neuropsychiatric Disorders (DIAMOND [103])

The DIAMOND is a well-validated, semi-structured diagnostic interview [103]. We will use the DIAMOND to confirm bipolar I or bipolar II disorder diagnoses, to assess episodes of major depressive disorder and diagnostic exclusion criteria (eating disorders, including symptoms consistent with other specified eating or feeding disorders; and for those with scores above the threshold on the AUDIT, DUDIT, or psychosis screener, the presence of alcohol use disorder, substance use disorder, or psychosis).

##### Columbia Suicide Severity Rating Scale screening version (C-SSRS; [113])

The C-SSRS is a brief, commonly used, semi-structured interview designed to cover suicidal ideation and behavior. We will use the C-SSRS to assess our active suicidality exclusion criteria.

##### Structured Clinical Interview for Sleep Disorders—Revised (SCISD-R; [82])

The SCISD-R is a semi-structured interview designed to diagnose common sleep disorders. We will use the SCISD-R to assess insomnia, hypersomnolence disorder and circadian sleep–wake disorders.

#### Primary outcomes

Our primary outcome measures will be: interview-based assessments of mood symptoms, and a brief self-report measure of Quality of Life, which were chosen based on strong psychometric characteristics, including high interrater reliability for the interview-based measures. Where possible, the symptom severity interviews will be conducted by raters who are unaware of the participant’s intervention status (which is feasible as our team is conducting a parallel study involving the Mediterranean diet). Where a rater becomes inadvertently aware of the intervention status, we will attempt to replace the interviewer for that participant.

##### Montgomery-Asberg Depression Rating Scale (MADRS; [114])

The MADRS is a brief measure designed to assess the severity of depressive symptoms.

##### Young Mania Rating Scale (YMRS; [87])

The YMRS is an 11-item interview designed to assess the severity of manic symptoms.

##### Quality of life

We will use the Brief Quality of Life in Bipolar Disorder (QoL.BD) questionnaire [90], which was designed to capture key life domains for individuals with BD and to be pragmatic for repeated assessments. The measure shows strong internal consistency and correlations with objective measures of functioning [109]. The brief short version is based on factor-analytic methods, has been validated for online use, and has been shown to be sensitive to change with intervention [115, 116].

#### Secondary outcome measures

To allow for more frequent and affordable assessments, we will supplement our core interviews with the Wellcome Trust recommended self-report measures for depression and mania: the Patient Health Questionnaire (PMQ-9 for mania and PHQ-9 for depression); [88, 89]. Both are brief scales that have been shown to have high internal consistency and to be sensitive to intervention effects. For comparison with the findings of other studies, we will also gather the Clinical Global Impression (CGI) and Patient Global Impression (PGI) indices.

##### Longitudinal Interval Follow-Up Evaluation (LIFE; [117, 118])

To provide more coverage of mood variability between assessment windows, we will also gather LIFE scores. We include the LIFE to enrich our ability to “catch” changes between follow-ups [111].

##### EMA of emotion states

In an optional add-on to the study, we will examine the temporal dynamics of mood with ecological momentary assessment (EMA) assessments. EMA has the advantage of providing a potentially more sensitive indicator of shifts in mood variability [119] that is less affected by recall bias. At baseline and again immediately after intervention, participants will be sent 5 surveys per day on their smartphones. Surveys will be randomly spaced, on average, 135 min apart to allow for three hours between the final survey of the day and their usual bedtime. Participants will have up to 80 min to respond to each survey and will receive reminders if they do not respond within the first 40 min.

In our EMA, we will use the Mood Zoom probes, which have been validated in BD [120]. Our core index derived from dimension reduction of the emotion probes is the mean variability in daily negative affect (mean square of successive difference). As a secondary test of proposed mechanisms, we will also assess whether TRE, as a circadian intervention, leads to decreased evening levels of arousal.

##### Broader clinical outcomes

To harmonize our findings with those of other Wellcome Trust grants, we included three measures as secondary outcome measures: the World Health Organization Disability Assessment Schedule 2.0—Brief (WHODAS 2.0-Brief; [93])**,** GAD-7 [121] and the panic, social anxiety and PTSD subscales of the Rapid Measurement Toolkit (RMT20; [122]). The WHODAS 2.0-Brief is a 12-item survey that assesses overall role functioning across major life domains. The GAD-7 is a commonly used measure of generalized anxiety symptoms. The RMT20 is a brief screening tool developed using IRT analyses and well validated against clinical diagnoses [122].

#### Potential mechanisms of change

As shown in Table 1, we will gather measures of potential change mechanisms at baseline and mid TRE. Our core hypotheses focus on diurnal clock gene amplitude, but we will gather a multi-modal battery of indices of circadian function (Fig. 1).

